## Abstract

**Background:**

Transitional-aged youth have a high burden of mental health difficulties in Canada, with Indigenous youth, in particular, experiencing additional circumstances that challenge their well-being. Mobile health (mHealth) approaches hold promise for supporting individuals in areas with less access to services such as Northern Ontario.

**Objective:**

The primary objective of this study is to evaluate the effectiveness of the JoyPop app in increasing emotion regulation skills for Indigenous transitional-aged youth (aged 18-25 years) on a waitlist for mental health services when compared with usual practice (UP). The secondary objectives are to (1) evaluate the impact of the app on general mental health symptoms and treatment readiness and (2) evaluate whether using the app is associated with a reduction in the use (and therefore cost) of other services while one is waiting for mental health services.

**Methods:**

The study is a pragmatic, parallel-arm randomized controlled superiority trial design spanning a 4-week period. All participants will receive UP, which involves waitlist monitoring practices at the study site, which includes regular check-in phone calls to obtain any updates regarding functioning. Participants will be allocated to the intervention (JoyPop+UP) or control (UP) condition in a 1:1 ratio using stratified block randomization. Participants will complete self-report measures of emotion regulation (primary outcome), mental health, treatment readiness, and service use during 3 assessments (baseline, second [after 2 weeks], and third [after 4 weeks]). Descriptive statistics pertaining to baseline variables and app usage will be reported. Linear mixed modeling will be used to analyze change in outcomes over time as a function of condition assignment, while a cost-consequence analysis will be used to evaluate the association between app use and service use.

**Results:**

Recruitment began September 1, 2023, and is ongoing. In total, 2 participants have completed the study.

**Conclusions:**

This study will assess whether the JoyPop app is effective for Indigenous transitional-aged youth on a waitlist for mental health services. Positive findings may support the integration of the app into mental health services as a waitlist management tool.

**Trial Registration:**

ClinicalTrials.gov NCT05991154; https://clinicaltrials.gov/study/NCT05991154

**International Registered Report Identifier (IRRID):**

DERR1-10.2196/64745

## Introduction

### Background

Transitional-aged youth refer to individuals aged roughly 15-26 years who are transitioning from childhood to adulthood, a time of developing independence and increased challenges [1]. In Canada, mental health difficulties among transitional-aged youth have increased across the past decade and during the COVID-19 pandemic [2,3]. Indigenous individuals within this age range experience a greater burden of mental health difficulties compared to their non-Indigenous peers [4,5], partly attributed to distal factors such as a family history of residential school attendance [6] and more proximal factors such as experiences of childhood adversity [7]. Stressors such as substance use, loss of culture, racism, socioeconomic status, and family instability also impact the well-being and mental health of Indigenous youth [8].

Mental health services are less accessible for youth living in remote and rural locations [9]. For instance, there is less use of outpatient-based mental health care and psychiatry services and higher rates of emergency department visits and hospital admissions for mental health-related reasons in Northern Ontario, a region of many different Indigenous communities [10]. In general, long wait times in Northern Ontario are similar to those experienced in other regions of the province [10]; however, wait times for counseling and therapy are particularly long in Thunder Bay compared to many other communities, with an average of 348 days [11]. Services that consider and incorporate culture are even more sparse. Long wait times for services not only delay care and contribute to prolonged distress and suffering but also affect interest and engagement in services once they are offered [12,13].

Mobile health (mHealth) innovations can increase access to mental health support. Specifically, smartphone apps can be an effective medium for improving mental health symptoms and quality of life [14,15] and for youth specifically [16]. Knowledge gaps exist, however, with respect to app effectiveness for those on a waitlist for services and for Indigenous youth. For instance, a recent review of waitlist interventions for youth did not include any app-based interventions [17]. Further, until recently, app evaluation studies seldom included Indigenous youth in the evaluations [18]. A review published in 2024 highlights several initial evaluations of apps with Indigenous youth that were focused on a variety of health-related outcomes, with a few of these focused on general mental health or coping and well-being [19]. Most of this research has been conducted with Indigenous populations outside of Canada, whose cultural values related to well-being may differ [20]. While there are apps geared toward Indigenous populations in Canada [21], they have not been evaluated among treatment-seeking youth, and some are primarily informational in nature or used for data collection only [22,23]. More research is needed to test the effectiveness of apps for addressing mental health among Indigenous youth [24].

In collaboration with an Indigenous-led agency informed by Anishinabek culture and located in Northern Ontario (Dilico Anishinabek Family Care; Dilico), in this study, the JoyPop app will be evaluated as a tool for supporting the mental health needs of Indigenous youth currently waiting for mental health services. The app was developed by researchers in collaboration with youth and service providers [25], and input from these stakeholders continues to inform its implementation and evaluation [26,27]. The app was designed to promote resilience to stress and adversity [25], targeting emotion regulation as part of this goal since it is linked to strengthening resilience [28]. Rather than targeting specific mental health diagnoses, focusing on emotion regulation is also in line with recommendations that apps target “transdiagnostic factors” to make the best use of resources [24], since difficulty with emotion regulation is common among different mental health concerns [29,30]. To accomplish this goal, app features include a mood rating feature to promote emotional awareness [31], breathing exercises to help with relaxation [32], relaxing sounds to help with sleep [33], a game and art feature helpful for distracting oneself from stressful situations [34,35], a journal focused on positive topics to promote well-being [36], and connection to one’s support network and professional helplines, if needed [37].

An initial evaluation of the JoyPop app showed that app use was associated with improvements in emotion regulation and depressive symptoms for transitional-aged youth starting university [38], who shared that they valued the opportunity to build awareness and regulation of emotions [39]. Another study conducted with an Indigenous community in Southern Ontario identified the potential utility of the app for youth in the community while also gathering knowledge on how cultural values were connected to the app features [26,27]. Prior to developing the current protocol, a pilot study was also conducted with Dilico and another local organization, in which youth identified benefits of using the app related to coping and mental health [40]. Service providers also expressed positive feelings about the app’s ease of use and how the app could be helpful for youth who are on the waitlist for services (eg, by increasing their comfort levels before services begin) [40].

In sum, it is important to identify beneficial transdiagnostic mental health supports for Indigenous transitional-aged youth in Northern Ontario. Considering past findings with the JoyPop app have been promising [26,27,38-40], a larger scale randomized controlled trial is warranted to more robustly evaluate its effectiveness. Providing this intervention while youth are on a waitlist for services may help reduce disengagement and the need to seek other services during this time.

### Objectives

The objectives of the study are in response to the goals and needs identified by the community partner, Dilico. Specifically, the primary objective is to determine the effectiveness of the JoyPop app compared to usual practice (UP) in improving emotion regulation among Indigenous transitional-aged youth (aged 18-25 years) who are awaiting mental health services. We hypothesize that youth receiving the app will show improvement in emotion regulation (small to medium effect) greater than that observed for youth receiving only UP.

The secondary objectives are to (1) compare change in mental health difficulties and treatment readiness between youth in each condition to better understand the app’s broader impact as a waitlist tool and (2) conduct an economic analysis to determine whether using the app while waiting for mental health services reduces other health service use and associated costs.

## Methods

### Overview of Study Design

This protocol was developed in collaboration with Dilico management and frontline staff to answer research questions of importance to the organization and the youth they serve. It was designed according to the Standard Protocol Items: Recommendations for Interventional Trials (SPIRIT) statement [41] (see Multimedia Appendix 1 for completed checklist). A pragmatic, parallel-arm randomized controlled superiority trial design will be used. Participants will be randomly assigned to the control (UP) or intervention (UP+JoyPop) condition in a 1:1 ratio using stratified block randomization. UP will involve waitlist monitoring practices at the study site, which include regular check-in phone calls to obtain any updates regarding functioning. In addition to UP, participants allocated to the intervention condition will receive the JoyPop app for 4 weeks and be asked to use it at least twice daily. Outcome measures will be administered to participants in both conditions during 3 assessments (first [baseline], second [after 2 weeks], and third [after 4 weeks]).

### Setting and Participants

Data collection will take place at Dilico Anishinabek Family Care, an Indigenous-led organization that provides culturally informed child welfare, mental health and addictions, and health services to Anishinabek children and adults. Programs and services are provided at individual, family, and community levels. This self-governed organization is situated in Fort William First Nation in Northern Ontario.

Youth will be informed about the study by waitlist case managers and with flyers and letters mailed and emailed to them. Youth will be eligible for trial participation if they are on the waitlist for mental health services at Dilico and between the ages of 18-25 years.

### Study Procedure

Table 1 describes participant progression through the study. A research assistant will contact interested youth by phone, text, or email to provide a brief description of the study. If a youth is interested and meets eligibility criteria, the research assistant will schedule their study orientation (as part of the baseline assessment). The research assistant will obtain informed consent during this orientation. As part of the informed consent process, youth will be made aware of local support services they can access should they experience distress during the study. They will also be made aware of the possibility that they are assigned to the control group so that they can make an informed decision about participation in light of this possibility.

**Table 1 table1:** Participant timeline.

		–1	T1	T2	T3
Activity/assessment		Pre-study screening	Orientation/baseline assessment	2 Weeks/second assessment	4 Weeks/third assessment
Eligibility screen		✓			
Informed consent and condition allocation			✓		
**Intervention (UP+JoyPop; or UP only)**					
	Outcomes measured: emotion regulation, mental health, treatment readiness, and service usage		✓	✓	✓
	Outcome measured: app quality				✓—intervention group only
	Control group participants given access to app				✓

Following consent, participants will complete the baseline assessment measures. They will be encouraged to respond as honestly and accurately as possible and not how they think researchers might want them to. Any participant that endorses suicidal thoughts during the first assessment will see an onsite counselor who will conduct a risk assessment and intervene as needed. Following completion of the assessment measures, the research assistant will access the allocation envelope from the locked filing cabinet, open it to determine the allocation, inform the participant, and proceed with associated study tasks. Participants allocated to the intervention condition will be supported in accessing and learning about the app. All participants will return to Dilico after 2 and 4 weeks to complete the second and third assessments. Once they have finished the study at the end of their third assessment, participants in the control condition will learn about and receive access to the app.

To promote retention, participants will receive reminders about upcoming assessments via text and email. To incentivize completion [42,43], participants will receive cash compensation (CAD $20 [US $13.89] for baseline assessment; CAD $25 [US $17.36] for second assessment (after 2 weeks); CAD $30 [US $20.83] for third assessment (after 4 weeks); and an additional CAD $25 [US $17.36] if all assessments are completed). We will arrange transportation (taxis, bus fare) if required for participants. Promising retention rates were observed using these methods in a pilot study [44].

### Description of Intervention and Control Conditions

Participants in the intervention condition will be able to use the JoyPop app by downloading it onto their own device (if suitable). Participants who do not have an iPhone will be given a refurbished one containing only the app to use for the duration of the study. Participants will be asked to use the app at least twice daily for 4 weeks. The JoyPop app has features that allow participants to rate their mood, engage in relaxation exercises (ie, breathing), prepare for sleep, journal, play a Tetris-like game, create art, and reach out to their support system or suitable helplines. Figure 1 further describes these features. Internet connection is not required to use the app.

**Figure 1 figure1:**
[figure not shown]
JoyPop features. LGBTQ: lesbian, gay, bisexual, transgender, and queer/questioning.

To promote engagement, youth will receive an email and SMS text message twice per day (at 8 am and 8 pm) reminding them to use the app. Outside of recommending using the app near the start and end of their day, we will not instruct or prescribe participants to engage with the app for any specific duration or pattern. Our intention is to evaluate the effects of using the app under real-world conditions in which users choose when and how often to use the app. Prior research suggests youth do use the app for the majority of the 4-week period [38,39]. Youth will also receive the usual waitlist management practice (UP).

Participants allocated to the control condition will only receive the UP. We chose this comparator to assess whether the JoyPop app could be a complementary support for individuals waiting for mental health services. This comparison creates the opportunity to test whether those who receive the app experience improved outcomes compared to those who do not receive it, representing “true” change after accounting for the regression to the mean phenomenon likely to affect both groups [45]. The use of a control condition addresses the limitations of our previous research in which all participants received the app [38].

### Randomization and Blinding

Stratified block randomization will be used to randomize participants to the control or intervention condition in a 1:1 ratio. An independent researcher outside of the research team will create the randomization sequence using a computer-generated sequencing tool [46] and then place allocations into numbered, opaque, sealed envelopes. These will be stored in a locked filing cabinet and only accessed by the research assistant who is with the participant.

To protect against bias, the principal and coinvestigators and the statistician conducting the analyses will be blinded to conditions. Trial participants cannot be blinded given the nature of this trial in which they are actively using the app or not. Research assistants will also not be blinded, as the condition assignment determines study procedures such as showing the participant how to use the app and providing them with the correct measures.

### Outcomes

The primary outcome is change in emotion regulation from the baseline assessment to the second assessment (after 2 weeks) and to the third assessment (after 4 weeks). Secondary outcomes are changes in mental health symptoms, readiness for treatment, and service usage from the baseline assessment to the second assessment and to the third assessment.

### Measures

#### Descriptive Measures

During the baseline assessment, participants will complete a demographics measure asking about their age, ethnicity, family composition, highest level of education, gender, sex at birth, sexual orientation, and living situation. Demographic variables that could change over time (ie, gender, sexual orientation, family composition, and living situation) will be reassessed at subsequent assessments. We will also measure symptom presentation during the baseline assessment using a modified version of the *DSM-5* (*Diagnostic and Statistical Manual of Mental Disorders* [Fifth Edition]) Self-Rated Level 1 Cross-Cutting Symptoms Measures (DSM-5-CCSM) [47] to characterize symptoms across 12 psychiatric domains (ie, depression, anger, irritability, mania, anxiety, somatic symptoms, inattention, suicidal ideation, psychosis, sleep disturbance, repetitive thoughts and behaviors, and substance use). One item pertaining to past suicide attempts was removed at the request of Dilico partners. Using the DSM-5-CCSM measure, respondents will report how much (or how often) they have been bothered by symptoms during the past 2 weeks. Items are rated on a 5-point scale (from 0=none at all to 4=severe or nearly every day) with the exception of items related to suicidal ideation and substance abuse, which are rated as either “Yes” or “No.” In a sample of adults receiving mental health services, most items in this measure except for the mania items have good test-retest reliability (intraclass correlation range=0.53-0.97) [48]. The measure also has good internal consistency (α=0.96) and criterion validity in terms of severity of impairment across life domains (*r*=0.84) in a community sample [49]. App usage data will be recorded in the JoyPop app with a timestamped record created each time the participant uses a feature.

#### Primary Outcome Measure

Emotion regulation will be measured with the Difficulties in Emotion Regulation Scale-Short Form (DERS-SF) [50,51], an 18-item self-report measure that asks respondents how often statements regarding their emotions have applied to them over the previous 2 weeks. Items are rated on a 5-point scale (ranging from 1=“almost never” to 5=“almost always”). Total scores range from 18 to 90, and subscale (strategy use, nonacceptance of emotion, impulsivity, ability to maintain focus on goals, awareness of emotions, and clarity of emotions) scores range from 3 to 15, with higher scores indicating greater difficulty regulating emotion. The DERS-SF demonstrates convergent validity via associations with symptoms of emotional disorders (eg, *r*=0.66 with the Beck Depression Inventory) [51,52]. In our pilot sample of Indigenous youth from Dilico, internal consistency for the total score ranged from α=0.87 to α=0.91 [53].

#### Secondary Outcome Measures

Mental health difficulties will be assessed with 2 measures: the Depression, Anxiety, and Stress Scale 21 (DASS-21) [54] and the Strengths and Difficulties Questionnaire (SDQ) [55,56]. The DASS-21 is a 21-item self-report measure that asks respondents how much specific statements regarding psychological distress applied to them over the past week. Items are rated on a 4-point scale (from 0=“never” to 3=“almost always”). Total scores range from 0 to 63, and subscale scores range from 0 to 21, with higher scores indicating greater distress. In clinical samples, this measure demonstrates convergent validity via correlations with other mental health measures (eg, *r*=0.85 between the Anxiety subscale and Beck Anxiety Inventory; *r*=–0.66 between the Depression subscale and Mental Health Questionnaire) [57,58]. In our pilot sample, internal consistency ranged from α=0.95 to α=0.96 across subscales. The SDQ is a 25-item self-report measure that asks respondents how true various statements have been for them. Items are rated on a 3-point scale (from 0=“not true” to 2=“certainly true”). Total scores range from 0 to 40, and subscale (emotional problems, conduct problems, hyperactivity, peer problems, and prosocial behavior) scores range from 0 to 10, with higher scores indicating greater difficulty (except for the prosocial scale for which the reverse applies). The SDQ has satisfactory internal consistency (α=0.80) and validity via its association with clinical diagnoses [56,59]. In our pilot sample, internal consistency was variable [53]; thus, we will ensure adequate psychometric performance in this study with a larger sample prior to analyses.

Treatment readiness will be assessed with the 4-item treatment readiness subscale of the Motivation for Youth’s Treatment Scale (MYTS) [60]. Items are rated on a 5-point scale (from 1=“strongly disagree” to 5=“strongly agree”), with the total subscale score calculated as the mean of item scores; higher scores indicate greater readiness. Groups with prior mental health service use and higher symptom severity tend to have higher average scores [60]. In our pilot sample, internal consistency ranged from α=0.80 to α=0.90.

Service usage will be assessed with 5 items generated by the research team that ask respondents how many times they accessed various health care services (ie, walk-in clinic, family doctor or nurse practitioner, emergency department, mental health counselor, and mental health hotline or phone support) over the previous 2 weeks.

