#### Secondary Outcomes

We will calculate change in mental health using total scores from the DASS-21 and SDQ, while we will calculate change in specific domains using the DASS-21 and SDQ subscale scores. We will calculate change in treatment readiness using the treatment readiness subscale from the MYTS as described. Similar to the primary outcome analyses, linear mixed modeling will be used to test whether the change in mental health symptoms and treatment readiness is greater for those in the intervention condition relative to those in the control condition by including an interaction term between time and group [61]. Covariates of gender and baseline mental health symptoms will again be included. With respect to service usage, we will estimate the costs of services used among participants in each condition and conduct a cost-consequence analysis to determine the incremental costs or savings associated with receiving the app [66].

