## Discussion

### Overview

The current research will explore the impact of the JoyPop app on emotion regulation, mental health, and treatment readiness among Indigenous youth waiting for mental health services. Positive change among these variables and demonstrated cost-effectiveness associated with using the app would support adopting the app into routine waitlist management practices within the current partner organization. The degree and magnitude of findings within this clinical sample of Indigenous youth will be compared to prior work within a non-clinical sample in which use was associated with positive change in emotion regulation and depression symptoms [38]. We will also compare findings to another trial studying the effectiveness of the app among younger Indigenous youth [69] and another with non-Indigenous youth [70]. Such comparisons will allow identifying how to best use the JoyPop app as a supportive tool. Finally, positive findings would also be consistent with a growing emphasis on transdiagnostic approaches to mental health care. Specifically, findings may increase our knowledge about the link between emotion regulation and various mental health–related difficulties among Indigenous youth [29].

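### The five-item service-use form cannot record hospital admissions or psychiatry visits, yet the cost analysis claims the app's incremental costs or savings without restriction

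*Protocol article*

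**What the plan says.** Under Secondary Outcome Measures, the protocol article states: "Service usage will be assessed with 5 items generated by the research team". The services are given in full: "ie, walk-in clinic, family doctor or nurse practitioner, emergency department, mental health counselor, and mental health hotline or phone support". Participants report the number of contacts "over the previous 2 weeks". Table 1 places the measure at baseline, 2 weeks and 4 weeks, so the two follow-up reports together cover the 4-week period.

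The Background describes the region's service use in two parts. On the low side, "there is less use of outpatient-based mental health care and psychiatry services". On the high side, it reports "higher rates of emergency department visits and hospital admissions for mental health-related reasons in Northern Ontario".

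The economic claims are broad. The second of the secondary objectives asks whether using the app "reduces other health service use and associated costs". Under Statistical Analyses, Secondary Outcomes, the team will estimate service costs by condition and "conduct a cost-consequence analysis to determine the incremental costs or savings associated with receiving the app". The Discussion (Overview) adds that "demonstrated cost-effectiveness associated with using the app would support adopting the app into routine waitlist management practices".

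**The concern.** The list of services is closed. It is introduced by *ie* rather than *eg*, it has five entries for five items, and there is no residual item for other services. The article describes no chart review, administrative linkage or other source for costing. Under Mitigation of Harms, serious adverse events go to the ethics board, but nothing connects those reports to the cost analysis.

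This is not a detail that can be left to an analysis plan, because no analysis can recover data that were not collected. Participants are waiting for mental health care, and the protocol provides for a risk assessment when suicidal thoughts are endorsed, so an admission during the study is possible. If one occurs, its inpatient cost is in neither arm's total. If admissions differ between arms, the reported incremental cost is wrong by that difference, while the objective and the conclusion read as though they cover health service use in general.

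**Working it through.** **Coverage.** The services named in the Background, set against the form:

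| Service in the Background | Regional direction | On the form? |
|---|---|---|
| Outpatient mental health care | lower | in part (counselor) |
| Psychiatry | lower | no |
| Emergency department visits | higher | yes |
| Hospital admissions | higher | no |

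Of the two services described as more used in the region, the form records one and omits the other.

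**Arm sizes.** The Sample Size section gives 66 analysed, 60% retention and 110 recruited. The inflation reproduces: 66 / 0.60 = 110. (The 66 also reproduces, at power 0.950, if the unstated correlation between repeated measures is taken as 0.5; nothing below depends on that.) With 1:1 allocation this is 110 / 2 = 55 randomised per arm and 66 / 2 = 33 expected completers per arm.

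**Effect of one unseen admission.** The document gives no unit costs. Assume CAD 5,000-15,000 per admission and CAD 300-500 per emergency visit. One admission in one arm shifts that arm's mean cost by C / n:

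- 55 randomised: 5,000 / 55 = CAD 91; 15,000 / 55 = CAD 273.
- 33 completers: 5,000 / 33 = CAD 152; 15,000 / 33 = CAD 455.

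In emergency visits per participant, the shift is 91 / 500 = 0.18 to 273 / 300 = 0.91 on 55, and 152 / 500 = 0.30 to 455 / 300 = 1.52 on 33.

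**How likely is an admission?** No rate is given. Assume a 4-week risk p of 0.5% to 5% per person.

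- Expected admissions among 66 completers: 66 × 0.005 = 0.33 to 66 × 0.05 = 3.3.
- Chance of at least one, 1 − (1 − p)^66: 28% to 97%.
- Among 110 recruited, expected admissions are 0.55 to 5.5.

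**Share of cost unseen.** Let R be the cost of an admission in emergency-visit equivalents (assumed 5 to 20) and o the cost per person of all recorded services in the same unit (assumed 0.5 to 4). The unseen share is pR / (pR + o).

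- Lowest: 0.005 × 5 = 0.025; 0.025 / (0.025 + 4) = about 1%.
- Highest: 0.05 × 20 = 1.0; 1.0 / (1.0 + 0.5) = 67%.

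The range is too wide to rank admissions against the recorded services.

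**The case against.** The strongest reply is that restricting a short, small trial to frequent contacts is a defensible choice of scope. Admissions will be few, and a single chance admission in one arm could dominate the incremental cost. Counting admissions might therefore reverse the comparison through noise just as omitting them might through bias. This stands as a reason to show totals both ways. It does not justify an unrestricted claim about costs or savings from a form that has no inpatient item.

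Other parts of the reply also stand:

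- The Background is regional context and names four service types together. A reader might infer that admissions and psychiatry are the region's distinctive service problem; the text does not say so, and the form covers emergency visits fully and outpatient care in part.
- Psychiatry is described as less used, so nothing shows that its omission matters much to cost over 4 weeks.
- A reader might infer that an admission through the emergency department will be costed as one emergency visit. The article does not state the costing rule; it says only that costs will be estimated. What is certain is that the form does not ask about the admission or the length of stay.
- The point concerns one part of the second of the secondary objectives. The primary outcome, the sample size and the effectiveness analyses are untouched.

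**Conclusion.** The point holds as a gap between the instrument and the claim. The form cannot record an admission or a psychiatry visit, no other costing source is described, and the objective, analysis and Discussion do not restrict the economic conclusion to the five services.

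Its size is unknown. The CAD 91-273 per randomised participant and CAD 152-455 per expected completer rest entirely on assumed unit costs and apply only if one arm has one more admission than the other. At an assumed 4-week risk of 0.5%, there is a 72% chance (100% − 28%) of no admission at all among the 66 completers; balanced admissions in equal arms would leave the incremental cost largely unchanged.

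A reader might go further and conclude that the plan misses its most expensive component, or that the comparison will point the wrong way. The document supports neither: it gives no unit costs, admission rates or cost shares, and the illustrative share runs from about 1% to 67%. This is an inexpensive improvement to a secondary analysis.

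**What to change.** Add one item to the form, with the same 2-week window: number of hospital admissions and nights in hospital. At lower priority, add an item for visits to a psychiatrist or other mental health specialist. Report each as its own line in the cost-consequence table, and give the cost totals with and without admissions, because a few events could dominate.

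If items cannot be added, reword the economic objective and the related conclusion so that they refer to the five listed services only, and state that inpatient and psychiatry costs were not measured.

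The cost of adding items is small: brief self-report questions, an ethics amendment, and probably review by the community partner, whose advisory committee approved all procedures and at whose request another item was removed. Participants already enrolled will lack the new items for visits they have completed. The Results section reports two completers as of July 2024 but does not say how many had been enrolled. The cost total including admissions will be more variable. The new items will also capture admissions only among participants who return for assessment.

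The wording-only remedy costs almost nothing but gives up the broader economic claim.
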